**Fig. 2 Fig2:**
[figure not shown]
Spirit checklist for the schedule of enrollment, interventions, and assessments

### Intervention description

The YRI is a culturally informed, 12-session, transdiagnostic group intervention that integrates core components of cognitive behavioral and interpersonal therapies as well as mindfulness techniques (i.e., psychoeducation, cognitive restructuring, behavioral activation, interpersonal effectiveness, problem-solving). Sessions typically last approximately 90 min each and incorporate both psychoeducation as well as activities and home practice to hone skills learned. The main objectives of the YRI are to improve emotion regulation, adaptive coping, and interpersonal skills (See Table 1). In the current study, the YRI will be delivered once per week during a time identified by schools when teachers and youth are available.

**Table 1 Tab1:** YRI Session Modules

Module	Components
1. Introductions and building group cohesion	• Introduces the format and goals of the intervention • Provides an opportunity to begin building trust, motivation for group participation, and group cohesion • Participants identify personal goals that group participation will help them achieve
2. Psychoeducation on Stress and Emotions	• Psychoeducation on traumatic stress reactions in order to normalize this experience for group participants • Participants learn about emotions, how to identify them and how this skill will help them reach their goals
3. Understanding the link between beliefs, bodies and behaviors	• Participants learn about the link between what you think, how it makes you feel, and how you behave • Participants identify healthy and unhealthy coping behaviors and discuss the impact of coping skills on reaching their goals
4. Taking control of your life	• Introduces concept of emotion-regulation and coping skills as one way of taking charge of your life • Practicing of coping strategies and recognizing things you can change and things you cannot • Processing loss and teaching emotion regulation strategies: behavioral activation and deep belly breathing
5. Relaxation and emotion regulation	• Participants reflect upon what types of behaviors can alter their mood for the better • Review of belly breathing and learn about guided imagery (safe spaces) • Participants identify fun activities that can disrupt negative thinking
6. Dealing with the past, things lost/things gained	• Focus on normative reactions to life disruption and loss related to traumatic experiences and loss • Participants reflect on things lost but also things gained in their lives
7. Sequential problem solving	• Participants learn how to approach decision-making using sequential (step-by-step problem-solving) • Practicing of sequential problem solving
9. Review of coping skills and problem solving	• Participants review and practice skills learned thus far • Participants learn another relaxation strategy: progressive muscle relaxation • Participants discuss use of the skills to attain their goals.
10. Addressing negative self-perceptions	• Interactive exercises are used show how negative beliefs affect their emotions and their behaviors • Participants learn strategies for changing their focus to the positive, including distraction by engaging in a fun or relaxing activity
11. Review of skills and relapse prevention	• Review of the skills learned in the group and planning for future challenges • The group will think about challenges in the future, review their warning signs for when they begin to feel upset, and discuss the strategies they have learned to help themselves feel better
12. Celebration and moving forward	• Reinforcing the important concepts mastered throughout the group process • Participants reflect on the information that they felt impacted them the most. • Participants have an opportunity to express appreciation of the things they have learned • Celebrations in the community are an optional component

### mHealth app development for mobile supervision

Drawing from best practices in user-centered design [28–30] and lessons learned from a prior pilot trial of an mHealth quality improvement app in Sierra Leone (NIMH MH124071), we are completing development of the mHealth supervision app that will also integrate WhatsApp as a communication platform. During an initial problem analysis phase, we convened one focus group discussion with teachers in Sierra Leone (*N* = 8) and one with YRI experts (*N* = 4) to determine how best to use WhatsApp to complement mHealth tools to facilitate supervision and fidelity monitoring. Focus groups sought to understand potential forms of 1- and 2-way communication, must-have functions to improve mHealth tools, how WhatsApp and mHealth tools can work together, and potential challenges of the mobile-based supervision model. We have incorporated information from the focus groups into design and development of an initial prototype. We will complete two rounds of iterative user experience/user interface testing with focus group participants to elicit “end-user” feedback while using mHealth tools prior to launching the clinical trial. Feedback from user testing sessions will inform final refinements of the integrated mobile supervision model.

### Settings and participants

We will recruit 50 schools from the Western region of Sierra Leone to participate in the hybrid type 3 implementation-effectiveness cluster randomized trial. The Western region of Sierra Leone comprises two districts: Western Urban and Western Rural. The capital city of Freetown is located in the urban area of the Western region. English is the official language, and Krio is the lingua franca. According to the Sierra Leone Demographic and Health Survey in 2019 data on educational attainment in the Western Area, over 55% of men and 48% women have attained some secondary education. According to the 2020 Annual School Census report, there are 240 senior secondary schools in the Western Area (77 in Western Rural and 163 in Western Urban), which account for over a third (36%) of all senior secondary schools in the country. Most schools are co-educational, and just over half are public schools.

We will aim for balance in recruitment of schools from urban and rural areas. Potential schools in the Western region will be identified through publicly available databases maintained by the Government of Sierra Leone’s Ministry of Basic and Senior Secondary Education (MBSSE). Trained research assistants (RAs) (who have completed CITI training and training in good clinical practice) will use recruitment scripts to explain the study to eligible participants and determine if they are interested in participating. School eligibility criteria are: (a) a secondary school in the Western region that is (b) willing to provide the YRI as an extracurricular activity. RAs will first recruit and enroll principals (*N* = 50). RAs will obtain informed consent from interested principals of eligible secondary schools.

Principals who consent and enroll will then provide lists of teachers in their school. RAs will recruit four teachers per enrolled school (*N* = 160; 80 female/80 male). Teacher inclusion criteria are (a) currently employed as a teacher in a secondary school in the Western Region; and (b) willing to provide the YRI as an extracurricular activity. RAs will aim for gender balanced recruitment of teachers from enrolled schools because the YRI is delivered by gender-matched facilitators. RAs will contact teachers to describe the study and invite them to participate. RAs will obtain informed consent from interested teachers who meet eligibility criteria.

We will recruit 480 youth from the 40 secondary schools randomized to receive the YRI delivered with mobile supervision and 480 youth from schools that will receive YRI delivered with standard supervision. We will enroll 240 youth from 10 control schools. We will aim to recruit 24 youth per school, with two YRI groups per intervention school. We aim to recruit an equal number of male and female participants, as the YRI is delivered in separate groups for males and females. The target sample size of 1200 youth is powered to account for 10–20% attrition per our prior experience in Sierra Leone. Youth inclusion criteria are: (a) currently enrolled in a secondary school in the Western region; (b) male or female aged 14–24; (c) able and willing to attend an extracurricular school activity. Parental consent and youth assent will be obtained for all youth under age 18.

Our target age for enrollment of youth (aged 14–24) is based on prior research on the YRI demonstrating that the intervention is effective with male and female populations within this age range [19, 20]. Including students 18–24 reduces potential bias towards those youth who take longer to complete secondary school, delayed entry into school, or dropped out of school and later returned. Excluding students older than age 24 ensures we are targeting the developmental window of youth as defined by the United Nations and the World Health Organization.

### YRI training and supervision

Following a train-the-trainer approach, we have hired a cadre of local experts previously trained in the YRI (*n* = 12) to conduct the two-week (10-day), in person YRI training with teachers who will deliver the YRI. Training will feature role playing, didactics, direct practice with the YRI manual, and group discussion. YRI experts will directly observe role plays of session modules and use the YRI fidelity checklist, a tool developed and tested in previous YRI trials, to rate fidelity to session content as well as competency during role plays and provide feedback. YRI trainees (teachers) will also complete a competency assessment at the end of training. Scores of > 70% will indicate YRI competency. For teachers scoring < 70%, YRI experts will provide “booster” training sessions targeting weakness identified in the competency assessment. Ten of the 12 YRI experts who deliver training will also serve as supervisors during the implementation phase. YRI supervisors and facilitators will complete a 1-day technology training led by the app development team and the Program Manager to address potential technology literacy challenges. YRI supervisors and facilitators will explore key features of the mHealth supervision app and WhatsApp through “hands on” testing/discovery and role-plays. The Program Manager will also review basic mobile phone functions and help troubleshoot any issues that arise.

YRI facilitators (teachers) in both study conditions will complete the fidelity and competency checklists after each session and audio record all sessions. Given the potential bias of self-report, supervisors will also code randomly selected 20-minute segments after each session. YRI fidelity checklists include both cross-cutting session items (e.g., encourages participation) to assess competency and session-specific items (e.g., facilitator reviewed deep belly breathing) to assess fidelity to content. Mobile-based supervision will include a designated 30–45 min weekly “supervision chat” using WhatsApp, review of audio taped session segments and fidelity and competency checklist data, as well as options for asynchronous messaging and chats as needed to provide targeted and supportive feedback, share lessons learned, and answer questions. Standard supervision will occur via weekly 30–45 min in-person sessions and include review and discussion of fidelity data. YRI facilitators who receive mobile-based supervision will complete the YRI fidelity and competency checklists as an electronic fillable form embedded in the mHealth app; those who receive standard supervision will complete a manual checklist in Excel uploaded to a secure server (Box).

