### Measures

#### Implementation outcomes

Feasibility, acceptability, appropriateness, adoption, sustainment, and organizational climate will be assessed via the Implementation Science Questionnaire developed at Johns Hopkins Bloomberg School of Public Health [34]. We have used these measures in prior research in Sierra Leone [20, 21], and the scales demonstrated strong psychometric properties (α = 0.79 − 0.90). The measures will be administered to youth, teachers and principals at baseline and post-intervention. Readiness for Implementing Change will assess readiness to change [35]. This measure has been used cross-culturally and has demonstrated strong psychometric properties (α = 0.94). These core constructs will also be probed via post-intervention key informant interviews with youth, teachers, and principals. We will administer the System Usability scale at post-intervention to assess mHealth app usability [36]. Fidelity will be assessed using the YRI fidelity checklists completed either via an electronic fillable form in the app (mobile supervision condition) or using Excel spreadsheets (standard supervision).

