### Data analysis

#### Quantitative analysis

We will compare fidelity trajectories of teachers receiving mobile supervision to those of teachers receiving standard supervision and investigate the null hypothesis that mobile supervision will not differ from standard supervision. We will conduct exploratory analyses to uncover typical trajectories for each supervision method (mobile-based or standard) and undertake comparisons using growth curve modeling by means of multilevel models [44]. We will use HLM software (v.8.2), which estimates multiple imputations based on the dependencies of multilevel data. Missing time points are addressed by the multilevel approach to growth modeling, and data from all enrolled participants can be analyzed in accordance with our intention to treat design. The null hypothesis is that the outcomes for the mobile supervision YRI groups will not differ from those in standard supervision YRI groups. With this approach, we can compare both YRI models (as identified by dummy variables) to the untreated control group or assess the null hypothesis of no difference between the fidelity in the two models (mobile-based vs. standard supervision).

We will also investigate the null hypothesis that mobile supervision will not differ from standard supervision at post-intervention in youth outcomes. To investigate YRI effects on mental health among youth at post-intervention, we will use multilevel models to accommodate the clustering of students within YRI groups. For analysis of student outcomes, student characteristics will be modeled in a level-one equation. The group characteristics will be modeled in the level-two equation. School characteristics will be incorporated into a third level.

However, we do not expect a significant school-level intraclass correlation (ICC) for targeted YRI outcomes. In the event we do not find a significant ICC, sector and rural/urban will be represented in the group-level equation, and a two-level model will be estimated.

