#### Statistical power analysis for fidelity to YRI implementation

To assess the minimal detectable effect size for the two-tailed null hypothesis of no difference for fidelity of groups receiving mobile versus standard supervision requires an estimate of the within-group ICC for fidelity for which there is no clear guidance in the literature. Given our standard assumptions, at a small to medium ICC of 0.2 for a two-tailed test with a null hypothesis of no difference for 80 groups and 12 fidelity ratings, the minimum detectable effect size would be 0.30, while at a large ICC of 0.5 the minimum detectable effect size would be 0.41.

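### The fidelity power statement makes no allowance for clustering by the ten supervisors, and the protocol does not say whether they work in one arm or both; if in one, the detectable effects are too small

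*Protocol article*

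**What the plan says.** In the protocol article, *Study design* randomises schools, 20 to each supervision model. *Settings and participants* gives two YRI groups per intervention school, hence 80 groups. *YRI training and supervision* names the people who deliver the supervision: "Ten of the 12 YRI experts who deliver training will also serve as supervisors during the implementation phase". The same section has teachers complete fidelity checklists after each session and adds, because self-report may be biased, that "supervisors will also code randomly selected 20-minute segments after each session".

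*Statistical power analysis for fidelity to YRI implementation* takes a two-tailed test with an ICC of 0.2 and states that "for 80 groups and 12 fidelity ratings, the minimum detectable effect size would be 0.30". With the ICC raised to 0.5, the printed value is 0.41. The section uses one ICC, for repeated ratings within a group.

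For the analysis of fidelity, *Quantitative analysis* says it will "undertake comparisons using growth curve modeling by means of multilevel models". It lists no levels for that model. The student, group and school levels in the same section are introduced for student outcomes.

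The article does not say whether a supervisor works in one arm or both, or whether teacher-completed or supervisor-coded scores are the analysed fidelity outcome.

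**The concern.** Groups that share a supervisor share part of how the supervision was delivered. Since supervision is meant to influence fidelity, their fidelity scores may be correlated whoever fills in the checklist. If supervisor-coded scores are analysed, the groups share a rater as well.

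If each supervisor belongs to one arm, supervisor variance is averaged over about five people per arm, not over 40 groups. Even a small supervisor share then adds noticeably to the variance of the arm contrast. Fidelity belongs to the first aim of this type 3 hybrid trial, and the hypothesis is that mobile and standard supervision are comparable. Standard errors that are too small could produce a spurious difference. Overstated power could make a non-significant result look like evidence of comparability.

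**Working it through.** **Inputs from the protocol article.** 10 supervisors; 40 intervention schools × 2 groups = 80 groups, so 40 per arm and 80/10 = 8 per supervisor; 12 ratings per group; ICC 0.2 or 0.5; two-tailed test. Power 0.8 and alpha 0.05 are stated only for student outcomes and are assumed to carry over to fidelity.

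**Assumed, because not given.** The supervisor share of total variance, *s*, is 0.01 to 0.05 and is taken out of the ICC so that total variance stays at 1. If supervisors are nested, there are five per arm with eight groups each. School-level correlation is left out to isolate the supervisor effect.

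**Step 1: the printed figures.** Var(diff) = (4/80) × [ICC + (1 − ICC)/12]; detectable effect = (1.960 + 0.842) × √Var.
- ICC 0.2: 0.05 × (0.2 + 0.0667) = 0.01333; SE 0.1155; effect 0.32 (printed 0.30).
- ICC 0.5: 0.05 × (0.5 + 0.0417) = 0.02708; SE 0.1646; effect 0.46 (printed 0.41).

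The printed values are not reproduced. A one-tailed multiplier gives 0.29 and 0.41. An unstated group-level covariate R² of about 0.20 to 0.25 would bring the two-tailed values to 0.30 and 0.41–0.42, but the article gives no such covariate. Two-tailed power at the printed effects is 0.74 and 0.70. The right baseline for judging supervisors is therefore 0.32 and 0.46.

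**Step 2: supervisors nested in arm.** Var(diff) = 2 × [*s*/5 + (ICC − *s* + (1 − ICC)/12)/40].

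Example, ICC 0.2 and *s* = 0.05: 2 × [0.01 + 0.21667/40] = 0.03083; SE 0.1756; effect 2.802 × 0.1756 = 0.49.

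| ICC | *s* | Effect, normal | Effect, t on 8 df | Type I error if supervisor ignored |
|---|---|---|---|---|
| 0.2 | 0.01 | 0.36 | 0.41 | 8% |
| 0.2 | 0.02 | 0.40 | 0.46 | 11% |
| 0.2 | 0.05 | 0.49 | 0.56 | 20% |
| 0.5 | 0.01 | 0.49 | 0.56 | 7% |
| 0.5 | 0.02 | 0.52 | 0.59 | 8% |
| 0.5 | 0.05 | 0.59 | 0.67 | 13% |

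The 8 df are 10 supervisors minus 2 arms. Type I error = 2 × [1 − Φ(1.96 × SE from step 1 / SE from step 2)]. For ICC 0.2 and *s* = 0.05 that is 2 × [1 − Φ(1.96 × 0.1155/0.1756)], about 0.20. Two-tailed power at the printed 0.30 (ICC 0.2) falls from 0.74 to between 0.64 (*s* = 0.01) and 0.40 (*s* = 0.05).

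**Step 3: each supervisor works in both arms, main effect only.** The *s*/5 term drops out of the contrast. With *s* = 0.05 the detectable effect is 0.29 (ICC 0.2) or 0.44 (ICC 0.5) once supervisor is modelled, below the 0.32 and 0.46 of step 1. Leaving supervisor out is then conservative.

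**Step 4: both arms, with a supervisor-by-arm variance *sx*.** Var(diff) = 2 × [*sx*/10 + (ICC − *sx* + (1 − ICC)/12)/40]. For *sx* = 0.01 to 0.05 the effect is 0.34 to 0.40 (ICC 0.2) and 0.47 to 0.52 (ICC 0.5).

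**The case against.** The strongest objection is that inflation depends on an allocation that the article never states. A reader might infer from ten supervisors and 80 groups that the fidelity standard errors and detectable effects are too optimistic as a matter of fact. The documents do not support that. If each supervisor serves both arms and is equally good in either mode, the error runs the other way (step 3). The technology training given to supervisors does not settle the allocation.

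Three further limits stand:
- A reader might infer that supervisors rate the analysed outcome. Teachers also complete the checklists, and the article does not say which score is analysed, so the rater effect applies only if supervisor codes are used. Clustering through shared supervision can arise with either score.
- A reader might infer that a supervisor term has been ruled out. None is described, but the random-effects detail may sit in an analysis plan that is not shown, and the student, group and school levels belong to the student-outcome model.
- Part of the gap from the printed 0.30 and 0.41 has nothing to do with supervisors, because the two-tailed baseline is already 0.32 and 0.46.

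The objection does not remove the point about the power statement. That is a printed claim, and its effective sample size depends on a supervision structure that the same article describes. Crossing does not fully protect it either: a supervisor may do better in person than by chat, or the reverse, and step 4 shows the consequence.

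**Conclusion.** The point holds in conditional form. The fidelity power statement ignores clustering by ten supervisors, and the article does not give the allocation needed to judge the consequence.

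With nesting in arm, the two-tailed detectable effect rises from 0.32 to 0.36–0.49 at ICC 0.2 (0.41–0.56 on 8 df), and from 0.46 to 0.49–0.59 at ICC 0.5 (0.56–0.67 on 8 df). An analysis that ignored supervisor would have a type I error of about 8% to 20% or 7% to 13% respectively. With supervisors in both arms, there is a problem only if their effect differs by arm, and it is smaller. These sizes rest on the assumed five-and-five split, eight groups per supervisor, and a supervisor share of 0.01 to 0.05, for which the article offers no source.

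**What to change.** 1. State whether each supervisor works in one arm or both, and which fidelity score (teacher-completed or supervisor-coded) is analysed.
2. Include supervisor in the fidelity growth model. If nested in arm, use a random supervisor effect with small-sample degrees of freedom. If crossed, use supervisor as a blocking factor with a random supervisor-by-arm component, since a blocking factor alone would not cover the interaction.
3. Restate the fidelity detectable effects from the correct two-tailed baseline, over a supervisor variance range such as 0.01 to 0.05. If a covariate or a one-tailed test lies behind 0.30 and 0.41, say so.

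The cost is wording in the analysis and power sections. The model needs only a record of which supervisor served each group, which should already exist. The price is less favourable detectable effects and, if supervisors are nested, few degrees of freedom for the arm comparison.
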